##### Analysis

Data for the different seizure vignettes will be analysed separately using an error components logit model that allows for a panel of responses from the same respondent. This will determine the importance of the different care attributes for preference and direction of effect (as indicated by the significance of the coefficients and their size). Comparison between vignettes will depend on attribute and level specification of each experiment. Analyses will be completed with and without respondents failing a ‘rationality’ test.

Marginal rates of substitution (the rate at which respondents are willing to give up a unit change in one attribute in exchange for a unit change in another while maintaining the same level of utility) will be calculated using each quantitative attribute as the value attribute with bootstrapped confidence intervals (1000 reps).

Preference heterogeneity will be assessed by estimating a mixed logit model, which will include random parameters for the attributes, and interactions between attributes and respondent characteristics.^91^ A-priori characteristics of interest are: (1) emergency care for epilepsy in the past 12 months (paramedic and/or ED visit), (2) social deprivation (with participants grouped according to how socially deprived the area is within which they live); (3) whether or not they have seen an epilepsy specialist within the prior 12 months (which they should have according to NICE guidelines^88^ given they will all have uncontrolled epilepsy); and (4) whether they or the person they know in the case of carers, self-reports an intellectual disability.

‘Utility scores’ for different ACP configurations and significantly different populations will be calculated and ranked accordingly. Their uptake under different seizure scenarios will be estimated.

All analyses will be conducted in STATA V.11.

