**Methods and analysis:**

Mixed-methods project comprising three-linked stages. In Stage 1, NHS bodies will be surveyed on ACPs they are considering and semi-structured interviews with PWE and their carers will explore attributes of care important to them and their concerns and expectations regarding ACPs. In Stage 2, Discrete Choice Experiments (DCE) will be completed with PWE and carers to identify the relative importance placed on different care attributes under common seizure scenarios and the trade-offs people are willing to make. The uptake of different ACP configurations will be estimated. In Stage 3, two Knowledge Exchange workshops using a nominal group technique will be run. NHS managers, health professionals, commissioners and patient and carer representatives will discuss DCE results and form a consensus on which ACP configuration best meets users’ needs and is NHS feasible.

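### Attribute importance is to be judged by the significance and size of coefficients, which gives no common scale across attributes, so statements on relative importance could be misordered

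*Protocol article*

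**What the plan says.** The Abstract of the protocol article gives one purpose of the discrete choice experiments as to "identify the relative importance placed on different care attributes under common seizure scenarios". The Analysis section under Stage 2b turns this into a rule. Each vignette is "analysed separately using an error components logit model that allows for a panel of responses from the same respondent", and this model is to show the importance of the attributes and the direction of their effect, "as indicated by the significance of the coefficients and their size".

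The same section plans three other outputs:

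- Marginal rates of substitution, described as "the rate at which respondents are willing to give up a unit change in one attribute in exchange for a unit change in another", and calculated "using each quantitative attribute as the value attribute with bootstrapped confidence intervals (1000 reps".
- Utility scores, which "for different ACP configurations and significantly different populations will be calculated and ranked accordingly".
- Estimated uptake of the configurations under each seizure scenario.

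Dependence on the chosen levels is acknowledged once, for a different comparison: "Comparison between vignettes will depend on attribute and level specification of each experiment". The article does not state how attributes will be coded, and it announces no formal ranking of attributes.

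**The concern.** The rule names two yardsticks, and neither measures relative importance across unlike attributes.

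- **Size.** If a quantitative attribute enters per unit, its coefficient is utility per hour, per mile or per day. That cannot be set against the coefficient of a yes/no attribute, and it changes when the unit changes. The article mentions several candidates of this kind: a follow-up call within 24, 48 or 72 hours (Introduction), distance travelled home (Stage 1c) and waiting time in the emergency department (Stage 2a).
- **Significance.** A z value grows with the number of respondents and with the spread of the levels. It says how well a coefficient is separated from zero, not how much the attribute matters.

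The two can also disagree, and the article does not say which prevails. At stake is the answer to a stated aim: what is reported about which features of post-seizure care matter most to patients and carers.

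**Working it through.** The disputed sentence carries no figure to reproduce. The check has an algebraic part, which needs no assumed preferences, and an illustration, which does.

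**1. Units.** Replacing x by kx changes the coefficient from b to b/k and leaves the fit and z unchanged. For the follow-up call, 1 day = 24 hours, so the per-day coefficient is 24 times the per-hour one.

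**2. When the two orders disagree.** Compare a yes/no attribute (coefficient c, range 1) with a quantitative attribute (coefficient b per unit, range R units). By size the yes/no attribute leads if |c| > |b|. By utility over the levels shown, the quantitative one leads if |b| × R > |c|. The orders therefore conflict whenever 1 < |c|/|b| < R. For a call at 24 to 72 hours, R = 72 − 24 = 48 in hours, or 2 in days. The zone of conflict is a ratio from 1 to 48 under one coding and from 1 to 2 under the other.

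**3. Illustration.** All preference values here are assumed: wait at 1, 3 or 6 h, −0.25 per h; specialist contact yes/no, 0.6; follow-up at 1, 2 or 3 days, −0.4 per day. The design uses 9 tasks (Box 1) and 116 respondents, which is two scenarios out of three for a subgroup of 174 (174 × 2/3 = 116). A simple logit without the error component was fitted to one simulated data set.

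| Attribute | Coefficient | z | Level range | Utility range | Share |
|---|---|---|---|---|---|
| Contact | 0.473 | 4.95 | 1 | 0.473 | 19.8% |
| Follow-up (days) | −0.351 | −5.96 | 2 | 0.702 | 29.4% |
| Wait (h) | −0.243 | −9.57 | 5 | 1.214 | 50.8% |

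Size gives contact, follow-up, wait. Utility range gives wait, follow-up, contact: the exact reverse. Significance here sides with utility range, so the rule's own two criteria conflict on one fit. The same reversal appeared with 84 and with 1,000 simulated respondents (wait's share 49.0% and 45.0%).

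**4. Recoding follow-up in hours.** Its coefficient becomes −0.351/24 = −0.0146, and it drops below wait in the size order. Unchanged are the z values, the log-likelihood (−646.46), the shares, and the utility difference between two configurations (1 h, no contact, 3 days against 3 h, contact, 2 days): 2 × 0.2427 − 0.473 − 0.3511 = −0.339.

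**5. Significance.** Means over 200 simulations:

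- Narrowing wait from 1–6 h to 1–2 h, with the same preference per hour, left its coefficient at about −0.25 but cut mean |z| from 9.8 to 2.2. Wait moved from most to least significant (contact 6.4, follow-up 7.0). Utility range falls too (0.25 × 5 = 1.25 to 0.25 × 1 = 0.25), so the order alone does not condemn z here.
- Changing only the number of respondents from 30 to 116 to 500 moved mean |z| for wait from 5.0 to 10.0 to 20.7, for contact from 3.0 to 6.1 to 12.7, and for follow-up from 3.3 to 6.6 to 13.6. Preferences were identical throughout. The z value is thus not a measure of strength, although its order held.

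**6. Marginal rates of substitution.** Dividing by the wait coefficient gives contact 0.473/0.243 = 1.9 h and follow-up 0.351/0.243 = 1.4 h per day. Dividing every coefficient by the same number keeps their order, and with follow-up in hours the second becomes 0.0146/0.243 = 0.06. These ratios are valid trade-offs with units attached, but they do not put whole attributes on one scale.

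**The case against.** The sentence can be read modestly: whether an attribute affects choice, in which direction, and how strongly within its own scale. No league table of attributes is announced, and the trade-offs promised beside relative importance in the Abstract are covered by the marginal rates of substitution. Coding is not stated. Box 1 anticipates at most three levels, so dummy or effects coding is possible, and such coefficients have no units. The article is a condensed account. Utility range is also only one defensible metric: it depends on the levels shown and, as a share, on which other attributes are included.

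Much of this stands. A reader might be tempted by three stronger readings that the documents do not support:

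- *That per-unit coefficients will certainly be compared with dummy coefficients.* The text treats some attributes as quantitative but does not fix the coding.
- *That sample size can reverse the order.* It moves attributes across the significance threshold, but in the simulations the order held in expectation.
- *That the ranking of pathways taken to the Stage 3 workshops is wrong.* That ranking is by utility score of whole configurations, which does not change with units (step 4).

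What does not stand is the defence that nothing is fixed. The article states a criterion for importance, and relative importance is its own declared aim. Even with fully dummy-coded attributes, significance would remain the wrong yardstick. The caveat on level specification covers comparison between vignettes, whereas this problem arises within each one.

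**Conclusion.** The point holds in a limited form. The stated criterion gives no common scale for relative importance, and following it could misorder the attributes within a vignette. The unit effect is exact (24-fold for a call timed in days rather than hours) but applies only where a quantitative attribute enters per unit. The full reversal in the illustration rests on assumed coefficients and levels and on a simplified model. It shows that misordering is possible, not that it will occur; step 2 gives the condition under which it does. The consequence is confined to statements about attribute importance. Utility scores, uptake estimates and the ranking of configurations are unaffected by units. The wording is worth changing before estimation, partly because settling the scale in advance removes a choice that could otherwise be made after seeing the coefficients.

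**What to change.** Replace the parenthesis in the Stage 2b Analysis section with a definition along these lines:

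*Within each vignette, the relative importance of an attribute is the difference in estimated utility between its best and worst level shown, optionally expressed as a share of the sum over attributes, with a confidence interval from a bootstrap that resamples respondents. It is conditional on the level ranges shown. P-values are used only to test whether a coefficient differs from zero.*

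Report this beside the marginal rates of substitution, with the unit of each stated. State how each attribute is coded once the levels are final. No new data are needed: the estimates are already produced and bootstrapping is already planned with 1,000 replications. The cost is a sentence or two and a few lines of code. The one drawback, dependence on the levels shown, is met by saying so wherever importance is reported.

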**Stage 2—Discrete choice experiments**		
Group 1 Patients	Clinically confirmed diagnosis of epilepsy (for any duration) Any epilepsy syndrome and any types of focal or generalised seizures Currently being prescribed antiepileptic medication Age≥18 years (no upper age limit) Have visited ED in the past 12 months for epilepsy Able to provide informed consent and independently complete a questionnaire in English Lives in the North West of England	Severe current psychiatric disorders (eg, acute psychosis) Life-threatening medical illness Resides within a care or nursing home or of no fixed abode
Carers	A significant other to a person with epilepsy (eg, family member, friend) who the patient identifies as providing informal support or self-identifies themselves if the patient has a substantial intellectual disability The person with epilepsy they care for has visited ED in the past 12 months Age≥16 years (no upper age limit) Able to provide informed consent and independently complete a questionnaire in English Lives in the North West of England	Severe current psychiatric disorders (eg, acute psychosis) Life-threatening medical illness
Group 2 Patients	Clinically confirmed diagnosis of epilepsy (for any duration) Any epilepsy syndrome and any types of focal or generalised seizures Currently being prescribed antiepileptic medication Age≥18 years (no upper age limit) Has *not* visited ED in the past 12 months, but has had a seizure with loss of awareness in this period Able to provide informed consent and independently complete a questionnaire in English Lives in the North West of England	Severe current psychiatric disorders (eg, acute psychosis) Life-threatening medical illness Resides within a care or nursing home or has no fixed abode
Carers	A significant other to a person with epilepsy (eg, family member, friend) who the patient identifies as providing informal support or self-identifies themselves if the patient has a substantial intellectual disability The person with epilepsy they care for has *not* visited ED in the past 12 months, but had a seizure with loss of awareness in this period Age≥16 years (no upper age limit) Able to provide informed consent and independently complete a questionnaire in English Lives in the North West of England	Severe current psychiatric disorders (eg, acute psychosis Life-threatening medical illness

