##### Recruitment

General Practices in North-West England will identify potential patient participants by searching their epilepsy registers.^86^ Practices will be recruited with the help of the NIHR Clinical Research Network North West Coast. Practices will send ostensibly eligible patients invitation packs via ‘Docmail’ and a repeat invite 2 weeks later to those not responding. Patients not wishing to participate will be encouraged to notify the team and detail their reasons. Eligibility criteria are in table 1.

A definitive sample size calculation depends on the finalised design of the DCE.^87^ To permit decisions regarding recruitment to be made in the meantime we anticipated the design and calculated the required sample size by using Orme’s^88^ formula. Full details are provided in box 1. This indicated 348 PWE (or associated informal carers) would be required, comprising data 174 patients (or associated carers) who have visited ED in the prior 12 months and 174 patients (or associated carers) who have not.

Box 1Sample size calculation for discrete choice experimentsFormula used and factors considered in estimating likely sample size requiredOrme’s formulae: (*n***t***a*)/ *c* must be ≥500, where *n* is number of respondents, *t* number of tasks, *a* number of alternatives per task, and *c* number of analysis cells (for main effects, the largest number of levels for any one attribute).Anticipated discrete choice experiments (DCEs) to involve participants being asked to make (*t*) nine separate choices between (*a*) two care packages and (*c*) three would be maximum attribute levels. Thus, Orme’s formula indicated complete data from n=84 needed.Intend to complete DCEs for three different seizure scenarios, but participants would only complete two, therefore 126 participants required.To allow for variation in the finalised number of choice tasks and levels we increased this to 150 and further inflated it to 174 to accommodate for ~15% of missing data experienced by prior epilepsy DCEs.As an objective was to describe and compare care preferences of two subgroups (patients (and associated carers) who have visited an ED in the prior 12 months versus patients (and associated carers) who have had a seizure in the prior 12 months, but have not visited an ED), 174 patients (and associated carers) who have visited ED in the prior 12 months and 174 patients (and associated carers) who have not, will need to be recruited.Total sample size, thus n=348.

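### The sample was doubled to compare ED visitors with non-visitors, but the listed analysis characteristic is paramedic and/or ED contact, and no listed term matches the recruited groups

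*Protocol article*

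**What the plan says.** The Stage 2 recruitment and sizing text uses one split throughout, ED visit or no ED visit:

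- Table 1, Stage 2, Group 1 patients: "Have visited ED in the past 12 months for epilepsy".
- Table 1, Stage 2, Group 2 patients: people who have not "visited ED in the past 12 months, but has had a seizure with loss of awareness in this period". Paramedic attendance without transport is not an exclusion.
- Box 1 (Stage 2b, Recruitment) gives the reason for doubling the sample: the objective was to "describe and compare care preferences of two subgroups (patients (and associated carers) who have visited an ED in the prior 12 months" with those who had a seizure but no ED visit.
- The Recruitment text sets the target as "174 patients (or associated carers) who have visited ED in the prior 12 months and 174 patients (or associated carers) who have not", and derives the number of general practices from the need for 174 ED visitors.
- Stage 2b Design uses the same split to decide who may complete the questionnaire face to face.

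The Stage 2b Analysis section then lists four a-priori characteristics for the heterogeneity model. The first is "emergency care for epilepsy in the past 12 months (paramedic and/or ED visit". The other three are social deprivation, specialist contact and intellectual disability.

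**The concern.** The two definitions differ for one identifiable set of people: those attended by paramedics in the past 12 months who did not go to ED. Recruitment puts them in Group 2, and the analysis variable puts them with the ED visitors. The movement is one way, because every Group 1 member has had an ED visit and stays in the exposed group.

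Two things are at stake. First, the contrast that justifies half the sample has no listed term, so the plan followed as written tests a different contrast. Second, the people who move have already had something close to what an alternative care pathway would offer, which is paramedic attendance without ED. Merging them with ED visitors hides whether their preferences differ. This carries forward, because utility scores are to be calculated for populations found to differ, and ranked configurations go to the Stage 3 workshops.

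**Working it through.** **1. Reproduce the plan's figure.** Inputs from Box 1: threshold 500, t = 9 tasks, a = 2 alternatives, c = 3 levels.

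- n = 500 × 3 / (9 × 2) = 83.3, rounded up to 84.
- Each participant completes two of three scenarios: 84 × 3/2 = 126.
- Box 1 raises 126 to 150 to allow for design changes, then to 174 for about 15% missing data. (150 × 1.15 = 172.5 and 150 / 0.85 = 176.5, so 174 lies between the two conventions.)
- Two groups: 2 × 174 = 348.

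The arithmetic holds. The problem is only in the grouping variable.

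**2. Apply the analysis definition to the recruited sample.** Let p be the paramedic-only share of Group 2. The document does not give it, so the values below are assumptions.

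- Analysed emergency-care group = 174(1+p).
- Analysed no-emergency-care group = 174(1−p).
- Share of the emergency-care group with no ED visit = p/(1+p).
- Complete respondents in the smaller group at 85% completeness = 174(1−p) × 0.85.

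| Assumed p | Analysed groups | Emergency-care group with no ED visit | Complete in smaller group (Box 1 minimum 126) |
|---|---|---|---|
| 0% | 174 v 174 | 0% | 147.9 |
| 5% | 183 v 165 | 4.8% | 140.5 |
| 10% | 191 v 157 | 9.1% | 133.1 |
| 15% | 200 v 148 | 13.0% | 125.7 |
| 20% | 209 v 139 | 16.7% | 118.3 |

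The minimum is crossed at p = 1 − 126/(174 × 0.85) = 14.8%. With Box 1's own ratio of 150/174 complete, it is crossed at p = 1 − 126/150 = 16%.

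**3. Gauge p roughly from the document.** The Recruitment text gives 24 adults per practice with a seizure in the year, 10 of whom visited ED, leaving 14. The Introduction says about 90% of ED attenders for seizures arrive by ambulance, so about 9 of the 10. It also says ambulance staff recommend conveyance for almost everyone they attend, without a percentage. Taking the conveyance rate as an assumption:

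- 95% conveyed: 9/0.95 − 9 = 0.47 people; p = 0.47/14 = 3.4%.
- 90% conveyed: 9/0.90 − 9 = 1.0 person; p = 1/14 = 7.1%.
- For p = 14.8%, paramedic-only people = 14 × 0.148 = 2.07, so conveyance would have to be 9/(9 + 2.07) = 81%.

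This treats contacts as people and a recommendation as a conveyance. Group 2 also requires loss of awareness, which shrinks the 14 and raises p. It is an order of magnitude only.

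**4. Effect of the imbalance on precision.** For a simple two-group contrast with a fixed total, the standard error rises by 1/√(1−p²): 0.5% at p = 10% and 2.1% at p = 20%.

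**The case against.** The best defence has four parts.

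- **The comparison is not ruled out.** Box 1 states the objective, group membership is fixed at recruitment, service use is collected, and the article condenses a fuller plan. A reader might infer that the ED comparison will never be run. The document does not support that; it shows only that no listed term runs it. But this is more than a detail left to a later plan, because the article does define the variable and defines it differently from the strata.
- **The share affected is probably small.** This stands. The Introduction's description of conveyance makes p = 15% or more hard to reach, so a reader should not infer that the subgroup sizing fails.
- **Orme's formula is a provisional rule of thumb for main effects.** This also stands. The Recruitment text says that the definitive calculation awaits the final design. The formula never guaranteed power for a subgroup contrast, and the planned model uses interactions, for which the loss of precision is about 2% even at p = 20%.
- **Paramedic and/or ED contact is a sensible construct.** The pathway begins with a 999 call and paramedic attendance, so this grouping is defensible in its own right. That supports keeping it, but not using it in place of the grouping that set the sample size.

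The Table 1 footnote that relaxes the criterion to ED or ambulance contact is attached to the Stage 1b interviews, so it does not reconcile the Stage 2 definitions.

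**Conclusion.** The mismatch is certain, because it rests on the text alone: recruitment and sizing use ED visit, the analysis uses paramedic and/or ED contact, and the two agree only if p = 0. Its size is uncertain and probably modest. At assumed p of 5% to 10%, about 5% to 9% of the analysed emergency-care group would have had no ED visit, and the smaller group would still have about 133 to 141 complete respondents against 126. The consequence is a contrast that is not the one planned and is mildly diluted. A sample-size failure would need p above about 15%, and nothing in the document points to that. All these figures rest on an assumed p and on 85% completeness.

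**What to change.** In the Stage 2b Analysis section, list ED visit in the past 12 months (yes/no, identical to Groups 1 and 2) as the a-priori interaction term for the comparison that Box 1 was sized for. Keep paramedic contact as an additional, separately labelled characteristic, for example with three levels: ED visit; paramedic contact only; neither. Make the change before the choice data are examined.

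The cost is about one line of wording. No new participants are needed, and service use is already collected; the questionnaire need only separate paramedic attendance from ED attendance. The small downside is one extra category, which may be sparse: at p = 5% to 10% it would hold about 9 to 17 people (174 × 0.05 = 8.7; 174 × 0.10 = 17.4), so it should be described rather than relied on for inference.
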